### Randomisation

Eligible participants will be randomised to one of the two treatment groups using permuted block randomisation with random block sizes of 3 and 6. An independent researcher will generate the allocation sequence and assignment will be revealed once eligibility has been confirmed using an online software (Study Randomizer) to ensure allocation concealment.^38^ Due to the nature of this study, it will not be possible to blind the participants, clinicians or the study team to the treatment allocation beyond this point.

### Intervention and control

#### Intervention: the record programme

The intervention comprises a moderately reduced-carbohydrate behavioural intervention, combining dietary advice, with structured written dietary information. It aims to improve participants’ adherence to the programme through a simple behavioural support programme, which includes goal-setting, planning, feedback and problem-solving. The intervention will be delivered during a 30 min session with a healthcare professional (HCP) during the baseline visit, where the intervention materials and advice will be provided, and will be supplemented with up to six brief telephone support sessions of up to 15 min depending on patient need. Participants in this group will be advised to follow the intervention until delivery.

This intervention was developed based on a review of the literature, study protocols, qualitative data of similar interventions and interviews with a diabetes-specialist dietitian, two obstetricians, a research midwife and a patient representative with previous GDM. A group of women affected by GDM, also helped to shape the ideas for this research, and to determine the questions we are trying to answer, and the type of dietary information and support they felt would be helpful.

The dietary component of this intervention consists of a moderately reduced-carbohydrate diet (130–150 g of total carbohydrate per day), with no additional energy restriction. This is in line with the dietary advice provided in previous GDM trials, as well as for women diagnosed with GDM at the hospital. The difference here is that the reduced-carbohydrate advice is given earlier in pregnancy, to assess whether it has benefits for women at increased risk of GDM. The core principles include:

REFRAIN from having sugary foods and drinks (eg, biscuits, confectionery, juice, sugary fizzy drinks), with the exception of dairy and limited fruit intake.REDUCE the amount of starchy carbohydrates to a moderate level, by having smaller portions of foods such as rice, pasta, bread, grains, potato, yams, cassava, plantain, at main meals.REPLACE refined starchy carbohydrates with wholegrain, unrefined versions, and sugary foods and drinks, with lower-carbohydrate, and lower, or no-sugar alternatives.

We anticipate that women in this study will consume more than the target 130–150 g of carbohydrate per day at baseline, but if the diet questionnaire reveals that a participant has carbohydrate intake already close to the recommended level, the advice given will ensure that their intake is maintained through healthy food choices in line with the RECORD diet principles. Standard healthy eating advice during pregnancy is also included, for example, high intake of vegetables, moderate intake of lean protein and guidance on foods that should be avoided during pregnancy. Information is discussed regarding the importance of controlling GWG, and women in this group are advised to weigh themselves once a week.

The development of this intervention was also informed by behavioural frameworks aiming to promote successful behaviour change. These are: the Capability, Opportunity and Motivation-Behavioural model, the Theoretical Domains Framework and the Behaviour Change Wheel.^39 40^ By using these frameworks, we targeted the components of psychological capability (eg, knowledge/understanding, skills, decision making, self-regulation), physical and social opportunity (eg, social influences and support, and environmental changes) and reflective motivation (eg, knowledge/understanding, confidence regarding capabilities, beliefs regarding risks, intentions, plans). To address these components, the intervention includes:

A consultation including the essential principles of the diet as described above, as well as the rationale behind the intervention and how it may work in controlling blood glucose levels, and attenuating GWG.Written resources to enhance participants’ confidence and skills in following the programme, and to facilitate decision making, including advice on food selection, meal and snack suggestions, and suggested recipes.Setting personalised realistic goals, by letting participant choose what changes they are comfortable making and the steps to achieve them. Participants can choose to use a ‘Personal action plan’ booklet to set their goals and reflect on their progress, as well as goal progression checklists, and self-weighing charts, however, these are also addressed during the support sessions.Structured HCP follow-up to provide support, contingency planning, problem-solving, planning of social support, advice on lapses and help with environmental or emotional triggers, and to provide feedback on progress. Additionally, participants are able to self-monitor their health via home finger-prick testing of their blood glucose and ketones, and by weighing themselves, which provides additional monitoring.Provision of feedback on progress and changes in clinical measures as a result of following the intervention, for example, GWG, capillary blood glucose and ketones, glucose curve from OGTTs, blood pressure.

#### Control

All women will receive routine antenatal care, which usually includes one-off face-to-face routine care NHS dietary advice during their booking appointment with a midwife. Anecdotal reports suggest this is focused on foods to be avoided during pregnancy for safety of the fetus, rather than healthy eating or weight control advice. This will have been given prior to randomisation in the study. Participants allocated to the control group will receive no additional advice beyond this.

### Patient and public involvement

We convened two focus groups with eight women recruited from the local antenatal clinic, national GDM support website and a social media forum. The first group helped to prioritise and refine the research question. In a second phase, women were provided with an outline of the study proposal, and were asked to provide further comments. From both phases, it was clear that women felt upset, shocked and anxious following a diagnosis of GDM, and highlighted a need for preventative interventions that could be implemented earlier in pregnancy. Participants also highlighted the importance of including neonatal outcomes in addition to the maternal outcomes. Women were interested in taking part in clinical trials aiming to prevent, treat or manage GDM, however, felt that that attending extra appointments for study visits and in particular having to use the parking at the hospital, would be a major barrier to participation. As a final stage, a patient representative provided feedback on the intervention materials to help make them clearer and more concise and continues to support the study team.

### Outcomes

#### Primary

The primary objective of this study is to test whether this reduced carbohydrate programme is feasible and leads to a reduction in carbohydrate intake in women who are pregnant and at risk of developing GDM. This feasibility measures will further determine whether to progress to a full RCT.

Progression criteria will be based on a traffic light system to decide whether to proceed to a full RCT (green), proceed with amendments for remediable issues (amber) or to not to proceed (red) (figure 2).^41^ The progression criteria will be:

Adoption of the intervention: that the intervention group reduces their total carbohydrate consumption by the time of follow-up, with green light for 95% CI of average intake that does not cross 170 g/day. (Evaluated as part of a broader assessment of dietary intake through an online 24-hour dietary recall questionnaire at the baseline and follow-up visits—detailed below).

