**Trial registration number:**

ISRCTN16235884.

STRENGTHS AND LIMITATIONS OF THIS STUDYThe intervention has been codeveloped by a multidisciplinary team of academic researchers and clinical professionals working in maternity, together with patients, to create a support programme likely to be acceptable to women and suitable for use in routine antenatal care.Quantitative and qualitative analyses will assess the feasibility (adherence and retention rate) and suitability of reducing carbohydrate intake in mid-pregnancy, to inform any progression to a future full trial.Dietary intake will be assessed at only two time points, and we will not be able to assess fluctuations in intake over time.This study is not powered to detect clinical effectiveness of the dietary intervention, and subsequent full-scale trials will be required to assess whether this intervention can effectively attenuate gestational weight gain and improve glycaemic control early in pregnancy, with the prospect of preventing gestational diabetes.

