### Sample size

This feasibility study is not powered to detect a statistically significant difference in clinical effectiveness between the trial arms. Instead, we will test for reductions in carbohydrate intake as preliminary evidence of the adoption of the reduced carbohydrate diet to an extent that is expected to alter health outcomes. The average total carbohydrate intake in women who are not pregnant is about 230 g/day.^34^ We have set the sample size to be able to detect a reduced target intake at 130–150 g, that is, ~140 g of total carbohydrate/day at follow-up, with 95% CI excluding 170 g/day. Progression criteria to a full trial also include adequate retention of participants as a measure of feasibility. We consider that a minimum of 80% of participants need to complete an OGTT at 24–28 weeks’ gestation, similar to previous trials, with 95% CI excluding 70%.^12 16^ Both progression criteria thresholds are satisfied with a sample size of 60 participants allocated in 2:1 ratio, intervention: control. Unequal randomisation allows us to have sufficient participants in the intervention arm for the qualitative study.

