### Retention and withdrawal

This study has been designed to run alongside routine antenatal appointments with remote support elements, to minimise the burden associated with attending extra visits. The brief telephone support sessions with a dietitian will act as prompts for the participants to engage with the intervention and self-monitoring. Participants are asked to attend one visit in addition to routine antenatal care. All of the women who take part would be offered an OGTT at 24–28 weeks of pregnancy for the diagnosis of GDM. The 24–28 weeks follow-up study visit and OGTT, replaces the routine care OGTT and the results are shared with the clinical care team. To compensate for the time and inconvenience in taking part, we offer participants financial incentives for their participation.

Each participant will have the right to withdraw from the study at any time, or may be withdrawn at the discretion of the research or clinical care team. Participants will have the right to withdraw their collected data if they wish. Withdrawn eligible and enrolled participants will not be replaced in this feasibility study. We will only replace participants whose baseline OGTT is abnormal, as they will have consented and been randomised before OGTT results become available, but they will have essentially failed the full screening.

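### The adoption criterion counts only RECORD women with a recall at the 24–28 week visit, so it leans towards green if those who leave eat clearly more carbohydrate

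*Protocol article*

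**What the plan says.** Under Outcomes, Primary, adoption is judged on mean total carbohydrate intake in the intervention group, "with green light for 95% CI of average intake that does not cross 170 g/day". The measurement is described as "Evaluated as part of a broader assessment of dietary intake through an online 24-hour dietary recall questionnaire at the baseline and follow-up visits". Table 1 marks the self-completed recall twice, at baseline and at the follow-up visit. The strengths and limitations box confirms that "Dietary intake will be assessed at only two time points", so a single recall after randomisation decides the criterion.

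Under Retention and withdrawal, women may leave at any time or be withdrawn by the research or clinical team, and "Withdrawn eligible and enrolled participants will not be replaced in this feasibility study". Only women whose baseline glucose tolerance test is abnormal are replaced.

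Under Sample size, the adoption target is "140 g of total carbohydrate/day at follow-up, with 95% CI excluding 170 g/day". The retention target is "We consider that a minimum of 80% of participants need to complete an OGTT at 24–28 weeks’ gestation", with a 95% CI that excludes 70%. Retention is counted over all participants in both arms and on availability of the glucose tolerance test. Statistical analysis promises descriptive statistics with 95% CIs for the progression criteria and names no analysis population for them.

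**The concern.** The primary objective asks whether the programme lowers intake in the women to whom it is offered. A mean over women who reached the visit answers a narrower question: whether those who stayed were eating less. The two agree if leaving has nothing to do with diet. They part if women who found the diet hard are also more likely to leave, because their higher intakes then vanish from the mean.

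Adoption is one of the two criteria that decide whether a full trial goes ahead, so a mean that is too favourable bears directly on that decision. It is also a matter of data collection. A later analysis plan can choose how to treat missing recalls, but it cannot recover recalls that nobody asked for.

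**Working it through.** **Inputs from the article.** N = 60 at 2:1, so 40 RECORD and 20 control women; target mean 140 g/day; bound 170 g/day; reference intake 230 g/day; retention 80% with bound 70%.

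**Assumptions.** The article gives no SD for carbohydrate intake; 60 g/day is used, with a range of 50 to 80. Leavers' intake is also assumed. The value of 230 comes from this sentence: "The average total carbohydrate intake in women who are not pregnant is about 230 g/day". It represents no adoption at all.

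**1. The plan's own figure.** The article states: "Both progression criteria thresholds are satisfied with a sample size of 60 participants allocated in 2:1 ratio, intervention: control".
- Retention: n = 1.96² × 0.8 × 0.2 / 0.10² = 61.5, so 62, close to 60.
- Adoption: a mean of 140 is green if t × SD/√n is below 30. The largest SD allowed is 30√n/t: 93.8 for n = 40, 83.2 for n = 32 and 78.9 for n = 29. Without a stated SD this leg cannot be reproduced further.

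**2. How much loss a green retention result allows.** For 48/60 the lower limit is 69.9% (Wald), 68.2% (Wilson) or 67.7% (exact), which is not green. Green needs 49/60 by Wald or Wilson, or 50/60 by the exact method. So 10 to 11 women may be lost. Because the arms are pooled, all could be RECORD women: 10/40 = 25% to 11/40 = 27.5%. Losing 8 RECORD and 3 control women leaves 49/60.

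**3. Main illustration: 8 of 40 lost, SD 60.**
- Attenders only (n = 32): 140 + 2.040 × 60/√32 = 140 + 21.6 = 161.6. Green.
- All 40, leavers at 230: mean = (32 × 140 + 8 × 230)/40 = 158.0. Sum of squares = 31 × 3600 + 7 × 3600 + 32 × 18² + 8 × 72² = 188,640, so SD = √(188,640/39) = 69.5. Upper limit = 158.0 + 2.023 × 69.5/√40 = 180.2. Not green.

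**4. Other values, same formulas, attenders at 140 g/day.**

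| Leavers of 40 | SD | Leavers' mean | Upper limit, attenders | Upper limit, all 40 | Changes? |
|---|---|---|---|---|---|
| 4 | 60 | 230 | 160.3 | 169.9 | no |
| 8 | 50 | 190 | 158.0 | 167.1 | no |
| 10 | 50 | 190 | 158.7 | 169.8 | no |
| 8 | 60 | 190 | 161.6 | 170.0 | borderline |
| 8 | 60 | 210 | 161.6 | 175.0 | yes |
| 8 | 50 | 230 | 158.0 | 177.6 | yes |
| 8 | 80 | 230 | 168.8 | 185.8 | yes |
| 11 | 60 | 230 | 162.8 | 187.7 | yes |

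With 8 leavers, setting the upper limit for all 40 equal to 170 gives a leavers' mean of about 190 g/day at SD 60 and between 201 and 202 at SD 50.

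**5. Chance of green (simulation, 40,000 runs).** With 8 leavers at 230 and attenders at 140, the chance is 0.78 if leavers are missing and 0.14 if they are measured (SD 50: 0.91 and 0.17; SD 80: 0.54 and 0.11). If the true mean of all 40 is exactly 170 and 11 leavers average 230, attenders average (40 × 170 − 11 × 230)/29 = 147.2. The chance of green is then 0.50 at SD 60 and 0.31 at SD 80, against a nominal 0.025. In a milder case, 8 leavers at 200, attenders average 162.5 and the chance is 0.10 at SD 60.

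**6. Loss unrelated to intake.** With a true mean of 140 and SD 60, the chance of green falls from 0.87 (n = 40) to 0.74 (n = 29).

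**The case against.** A reader might infer that attrition by itself can buy a green light. It cannot: step 6 shows that random loss makes green harder. The article also has a second criterion aimed at loss. A uniform 20% loss (48/60) would not be green on retention, so the main illustration passes both criteria only if control loss is lower, at most 3 of 20. The Process outcomes report attendance by group, so such an imbalance would be seen. The limit is real but loose, because it pools the arms and because a completed glucose tolerance test does not guarantee a recall.

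A reader might also infer that women who stop the diet are dropped from follow-up. The article does not say so. Study procedures invites all confirmed eligible participants to the second visit, with no condition on adherence. A woman who gives up the diet and still attends is counted.

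Nothing in the article shows that leavers will be the women who failed the diet. The barriers it reports are extra appointments and hospital parking. Counting every leaver at 230 is the severe end, and the table shows milder cases that do not change the result.

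Finally, a rule for missing recalls and levels of withdrawal may sit in a full protocol or analysis plan that is not shown. Their absence from the article is not an error. The online recall could also be completed away from the visit. However, the outcome definition and Table 1 place it there, and the article makes no provision for non-attenders.

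**Conclusion.** The point holds conditionally. As defined, adoption is measured only in RECORD women who reach the follow-up recall, and the retention criterion does not fully protect it. The bias runs towards green only if leavers eat clearly more than attenders. With 8 of 40 lost and attenders on target, that means roughly 190 g/day or more at SD 60, or just over 201 at SD 50. At the severe end (leavers at 230, SD 60) the upper limit moves from 161.6 to 180.2 g/day, across the 170 threshold. With few leavers, or leavers at 190 with SD 50, the decision does not change. The SD and the leavers' intake are assumptions. Figure 2, which should hold the amber and red bands, is not shown, so the effect on the overall progression decision cannot be fixed exactly. The change is worth making because it is cheap and concerns data that cannot be collected later.

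**What to change.** In Outcomes, Primary, and in Carbohydrate consumption:

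1. Send the online Intake24 recall at 24–28 weeks to every eligible randomised woman who has not withdrawn consent to data use, whether or not she attends the visit or still follows RECORD.
2. Define adoption over all eligible women allocated to RECORD, and report recall completion by arm.
3. Next to the observed mean and its 95% CI, show a sensitivity analysis with missing intakes set first to the woman's own baseline recall and then to about 230 g/day, and state whether green survives each.

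Baseline substitution should stay a sensitivity analysis and not become the deciding rule. It is a single imputation that treats filled-in values as observed. The Intervention section also allows that some women start near the target, and for them it would count a leaver as an adopter. Showing both values covers this.

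The cost is a few sentences, a reminder message with an existing link, and one extra summary. The downside is that a green result may look less secure.

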**Figure 2 F2:**
[figure not shown]
Progression criteria. OGTT, oral glucose tolerance test.

Retention rate: proportion of all participants who complete an OGTT at the follow-up time point, with green light for 95% CI of average completion rate that does not cross 70%. (Evaluated by documentation at 24–28 weeks’ gestation; assessed as the proportion of participants for whom OGTT measurements are available).

#### Secondary

Change in fasting plasma glucose, 1-hour and 2-hour glucose. (OGTT at baseline and follow-up visit).Change in glycated haemoglobin (HbA1c), fasting plasma insulin and insulin resistance (Homeostatic Model Assessment of Insulin Resistance-HOMA-IR). (Blood samples collected as part of OGTT at baseline and follow-up visit).Proportion of participants who are diagnosed with GDM. (Documentation at baseline and follow-up visit).GWG: weight change from baseline until before delivery. If predelivery weight is not available, we will use weight at 36 weeks’ gestation collected as part of routine practice.Proportion of participants meeting the Institute of Medicine recommendations for GWG.^42^
Dietary intake: total carbohydrate intake (g/day) and total energy intake (MJ/day), percentage of daily total energy intake from carbohydrates. (Dietary composition analysis at baseline and follow-up visit—see details below)Distribution of fasting capillary blood glucose and ketone levels across gestational age from baseline until before delivery.

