### Recruitment

Participants will be recruited from one maternity care centre in Oxfordshire, UK. The study is expected to run from May 2021 to December 2022. Women attending the dating or nuchal ultrasound scan appointment (typically between 8 and 14 weeks’ gestation) will be approached to take part in the study. Potentially eligible participants will be provided with the participant information sheet, and invited to give their contact details. A member of the research team will contact the women who were interested in taking part to discuss the study and assess self-reported eligibility to participate according to the full inclusion and exclusion criteria as detailed below. Eligible individuals who wish to participate will be booked in for a face-to-face baseline appointment. The aim is to recruit women as early in pregnancy as possible, therefore, we will aim to book the baseline appointment for the trial within 2 weeks after the dating scan. However, we recognise this extra appointment at short notice may be challenging, and during this feasibility trial we will allow women to attend their baseline appointment up to 20 weeks’ gestation. This allows at least a month to practise the dietary changes and assess whether the progression criteria are met. In addition, we will monitor the timing of the baseline appointment to check whether setting a limit at 14 weeks’ gestation for recruitment to any future definitive trial, would be feasible. For those who decline to participate, permission will be sought to record the barriers to participation.

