### Eligibility criteria

#### Inclusion criteria

Pregnant women <20 weeks’ gestation.Aged ≥18 years.BMI ≥30 kg/m^2^ measured at booking appointment.Planned antenatal care and delivery at the study setting.

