### GDM diagnosis

Participants who develop GDM or who are diagnosed with GDM at the 24–28 weeks’ follow-up visit, will be referred to the clinical care team and offered the current standard medical treatment. In line with the NICE guidelines, this includes monitoring of blood glucose (two of the fasting measurements will continue to be used in the study), and diet and physical activity advice for the management of GDM.^36^ More specifically, women with GDM are advised to manage carbohydrate intake, to limit their weight gain until delivery, and are encouraged to do 150 min of moderate intensity activity per week. Women in the intervention group, can choose to continue following the RECORD programme until delivery (at the discretion of the clinical care team). Women in the control group will receive advice to reduce their carbohydrate intake at this stage, and this will be noted. All participants with GDM, will be encouraged to continue monitoring their ketone levels twice a week for the remaining of pregnancy.

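### Gestational weight gain is a raw kg change over a span of about 16 to 30 weeks with two possible end weights, so women are not comparable on it and the arm comparison gains avoidable noise

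*Protocol article*

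**What the plan says.** All references are to the protocol article.

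- **Outcome.** Outcomes, Secondary, defines gestational weight gain as "weight change from baseline until before delivery. If predelivery weight is not available, we will use weight at 36 weeks". The next item is "Proportion of participants meeting the Institute of Medicine recommendations for GWG". No start weight is named for that classification.
- **Start point.** Under Recruitment, women are approached at a scan "typically between 8 and 14 weeks’ gestation". The aim is that "we will aim to book the baseline appointment for the trial within 2 weeks after the dating scan", but "we will allow women to attend their baseline appointment up to 20 weeks’ gestation". Study design puts the limit at 19 weeks plus 6 days.
- **Order of events.** Study procedures lists weight among the baseline assessments completed before randomisation at the same visit.
- **Other weights.** Eligibility BMI is "measured at booking appointment". Table 1 has both arms weighed at baseline and at the 24–28 week visit. Physical measurements says this is done on a study digital scale.
- **GDM care.** Under GDM diagnosis, women with GDM in either arm are offered standard care, including advice to manage carbohydrate and limit gain until delivery. For controls, "Women in the control group will receive advice to reduce their carbohydrate intake at this stage, and this will be noted". Intervention women may stay on the programme.
- **Analysis.** Statistical analysis plans descriptive comparisons with 95% CIs, including differences in means or proportions between the two groups.

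**The concern.** A change in kilograms means the same thing in two women only if it covers a similar length of pregnancy. Here the start depends on when the baseline visit could be arranged, and the end on which late weight happens to exist. A woman seen early and weighed just before delivery will show far more gain than one seen near 20 weeks and last weighed at 36, even at an identical rate.

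The article names attenuated gain as one possible benefit of the diet, and the potential effect on it is a stated objective. A mean difference with an interval will be reported and is likely to inform the design of a full trial. Variation that comes only from weighing dates widens that interval and carries no information about the diet. The guideline proportion has the same weakness if it is built on the same gain.

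**Working it through.** The plan states no figure for gestational weight gain, so there is none to reproduce.

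**Inputs from the article:** latest baseline 19+6 = 19.86 weeks; fallback end weight at 36 weeks; 60 women at 2:1, so 40 and 20; GDM prevalence of 25–30% in women with obesity (Introduction).

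**Assumed inputs:** early baseline at 10 weeks; delivery at 40 weeks; gain of 0.2 to 0.5 kg/week, roughly linear.

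**1. Span between women.**
- Shortest: 36 − 19.86 = 16.1 weeks.
- Longest: 40 − 10 = 30 weeks (32 from a baseline at 8 weeks).
- Ratio: 30 / 16.1 = 1.9.
- Difference at an identical rate: 13.86 weeks × 0.2 = 2.8 kg; × 0.5 = 6.9 kg.

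**2. End-point switch alone** (36 v 40 weeks): 4 × 0.2 = 0.8 kg; 4 × 0.5 = 2.0 kg.

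**3. Chance difference between arms.** Take baseline as uniform over 10 to 19.86 weeks, half the women on the 36-week fallback, and the rest weighed uniformly over 37 to 41 weeks.
- Variance of start: 9.86² / 12 = 8.10.
- Variance of end: 0.25 × 3² + 0.5 × 4² / 12 = 2.92.
- SD of span: √11.02 = 3.3 weeks.
- SE of the arm difference: 3.3 × √(1/40 + 1/20) = 0.90 weeks, so the 95% chance range is about ±1.8 weeks around an expected difference of zero.
- In kg: 1.77 × 0.2 = 0.35; 1.77 × 0.5 = 0.89.

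Simulation with 30%, 50% and 70% on the fallback gave 95% ranges of ±1.74 to ±1.78 weeks.

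**4. When bias could arise.** Suppose a predelivery weight were available 20 percentage points more often in one arm. The arm means would shift by 0.20 × 3 weeks × 0.2 = 0.12 kg up to 0.20 × 4 weeks × 0.5 = 0.40 kg.

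**5. GDM care inside the span.** At 25–30%, 5 to 6 of 20 controls have GDM and, with no effect of the diet, 10 to 12 of 40 intervention women. Assume care slows gain by 0.1 to 0.3 kg/week over 8 to 16 weeks.
- Control mean falls by 0.25 × 8 × 0.1 = 0.2 kg up to 0.30 × 16 × 0.3 = 1.4 kg.
- The contrast moves less, because the intervention arm is treated too. If GDM were 39% lower there (the reduction the Introduction cites for one earlier trial, borrowed as an assumption), the shift is 0.39 of those values, about 0.1 to 0.6 kg.

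**6. Gain left out by a late baseline.** Against an assumed start at 10 weeks: 9.86 × 0.2 = 2.0 kg up to 9.86 × 0.5 = 4.9 kg. This matters only if the classification starts at the baseline visit.

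**7. Effect of dividing by weeks.** At 0.3 kg/week, 16.1 weeks gives 4.8 kg and 30 weeks gives 9.0 kg. Both return 0.3 kg/week.

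**The case against.** The strongest reply has four parts.

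- **Randomisation protects the comparison.** Baseline weight precedes allocation, so start timing is balanced in expectation. This stands. A reader might infer that the arms are not comparable, but the article gives no evidence that delivery timing or availability of the predelivery weight differs by arm. That bias is possible, not shown.
- **GDM care is not confined to controls.** This also stands. A reader might take the control-arm sentence as one-sided treatment, but women with GDM in both arms receive advice on carbohydrate and weight gain. Only the new advice to reduce carbohydrate is particular to controls. Comparing arms regardless of that care is a legitimate question, and it fits an intervention followed until delivery.
- **The 24–28 week weight is not simply cleaner.** Its span runs from 24 − 19.86 = 4.1 weeks to 28 − 10 = 18 weeks, more than fourfold. On Table 1's nominal schedule it covers 12 of 24 weeks. This stands against making it the main measure, but not against reporting it as a supplement.
- **Adjustment is often left to an analysis plan, and the outcome is minor.** Missing analysis detail is not the point here. The article itself fixes a raw change with interchangeable end weights. The low stakes are accepted and limit the severity.

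**Conclusion.** The definition should be improved. The span varies about twofold between women. That is worth 2.8 to 6.9 kg at an identical rate of gain, and the end-point switch alone is worth 0.8 to 2.0 kg. These are differences between extreme cases, not expected effects on group means, and they rest on assumed rates and gestations. Between arms the consequence is mainly noise, about ±0.35 to 0.9 kg, with bias only under the conditions in step 4.

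On the guideline outcome, a reader might conclude that too few women will be classed as exceeding the recommendation. The article does not support that. It does not say which start weight is used, it does not give the ranges, and the outcome is the proportion meeting the recommendation, which omitted gain could move either way. What holds is that the start weight is unstated and that using the baseline visit may misclassify women seen late.

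Severity is low to moderate. This is a descriptive secondary outcome in a trial not powered for effectiveness, and neither progression criterion depends on it.

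**What to change.** - **Main late-pregnancy measure.** Use the 36-week weight as the common end point. Report kg per week between the two dated weights, or adjust the arm difference for baseline weight and weeks elapsed. With a 36-week end point, weeks elapsed depends almost entirely on gestation at baseline, which precedes randomisation. Keep predelivery weight as a sensitivity analysis.
- **Guideline classification.** Start from the booking measurement already used for the eligibility BMI, or classify on weekly rate, and say which.
- **Supplementary measure.** Report change from baseline to the 24–28 week visit, adjusted for weeks between visits. It is largely free of GDM care started after the follow-up OGTT.
- **Later care.** State that the late-pregnancy comparison is made regardless of GDM care, which both arms receive.
- **Source of the 36-week weight.** Process outcomes places it at a hospital appointment and Physical measurements at the primary care practice. Reconcile the two.

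The cost is outcome wording, recorded weighing dates and one extracted booking weight. The downsides are small. Booking and 36-week weights are not on the study scale, a 36-week end point drops the last weeks of gain, and women who deliver before 36 weeks need a stated rule. A weekly rate also assumes roughly linear gain, which is a reason to show the adjusted difference as well.
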